#### Primary outcome measure

For the primary outcome, return to sport is determined based on a composite of answers to 4 questions (Additional file 1), which we have refined based on our previous research [19, 35, 36].

To be classified as returned to the preinjury sport *and* level (i.e. *yes* for the primary outcome), participants must have answered *I have returned to the same sport as before injury* to question 1, AND *I have returned to full training and modified competition* or *I have returned to full training and full competition* to question 2, AND selected the same sport as they played preinjury at question 3, AND selected the same level as they played before injury at question 4 (to ensure accuracy, we cross-check answers to question 3 and question 4 at 12 months, against the baseline data).

#### Secondary outcome measures: *sports participation*

Participants self-report the activity or activities (participants can register up to 3 separate activities) they participated in during the registration period (preceding two weeks). Participants select an activity from a list of 19 sports; there is also an option to specify an unlisted activity. Participants report the number of minutes they participated in each activity during the registration period, and the total number of physical activity sessions including, but not limited to knee rehabilitation sessions, active recreation, training/practice and competition.

#### Secondary outcome measures: *new knee injuries*

Participants self-report any new knee problems that have occurred during the registration period (preceding two weeks). We use an ‘all complaints’ definition of injury [37]. Participants describe the problem, and any diagnosis and treatment received (including the clinician and/or institution where diagnosis and/or treatment was provided).

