**Methods:**

Participants scheduled for primary ACL reconstruction are recruited prior to surgery from one of six trial sites in Sweden. We aim to recruit 222 participants (111 in each group) for the BANG trial. Participants are randomly allocated to receive either usual rehabilitation care alone or usual rehabilitation care plus the Back in the Game smartphone application intervention. Back in the Game is a 24-week Internet-delivered programme, based on cognitive-behavioural therapy. The primary outcome is return to the preinjury sport and level at 12 months follow-up. The secondary outcomes assess physical activity participation, new knee injuries, psychological factors, quality of life and physical function. Physical activity participation and new injuries are self-reported every two weeks for 12 months, then every 4 weeks to 24 months follow-up. Psychological readiness to return to sport, knee self-efficacy, motivation to participate in leisure time physical activity, knee-related quality of life, and self-reported knee function are also assessed at 3, 6, 9, 12 and 24 months after surgery. A clinical assessment of strength, knee range of motion, effusion and hopping performance is completed by a blinded assessor at 12 months to assess physical function.

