**Fig. 1 Fig1:**
[figure not shown]
Flow of participants through the trial. Fortnightly physical activity and injury registration in the first year of follow-up, and monthly physical activity and injury registration in the second year of follow-up are not shown

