### Outcomes

The primary outcome is the proportion of participants who return to their preinjury sport *and* participation level at 12 months. The secondary outcomes (Table 2, Additional file 1) are measured at clinically-relevant times, and reflect a biopsychosocial approach to outcome evaluation: patient- and clinician-reported knee function, sports participation and new knee injuries for the biological aspect, psychological readiness to return to sport and self-efficacy for the psychological aspect, adherence to the intervention and/or rehabilitation, and a range of baseline characteristics (Table 3, Additional file 1) for the social aspect.

**Table 2 Tab2:** Summary of secondary outcomes

Measurement variable	Aggregation method	Measurement time point(s)
Sports participation	Number of minutes playing (i) contact, pivoting sports, (ii) non-contact, pivoting sports, (iii) non-pivoting sports	Every 2 weeks to 12-months follow-up; every month from 12 to 24 months follow-up
New knee injuries	Proportion of participants who report a new (i) ACL injury, (ii) meniscus injury, (iii) other knee injury or problem	Every 2 weeks to 12-months follow-up; every month from 12 to 24 months follow-up
Psychological readiness to return to sport	Mean or median ACL-Return to Sport after Injury scale [24] score	3, 6, 9, 12, 24 months
Knee-related self-efficacy	Mean or median Knee Self-Efficacy Scale [25] future domain score	12, 24 months
Motivation to return to sport [26]	Median	3, 6, 9 months
Knee-related quality of life	Mean or median ACL-Quality of Life scale [27] score	12, 24 months
Self-reported knee function	Mean or median International Knee Documentation Committee subjective knee form [28] score	6, 12, 24 months
Self-reported knee function	Mean or median Single Assessment Numeric Evaluation [29]	Every 2 weeks to 12-months follow-up; every month from 12 to 24 months follow-up
Functional knee stability	Frequency of giving way episodes	12, 24 months
Knee effusion	Proportion of participants with stroke test [30] score: 0, trace, 1+, 2+, 3+	12 months
Hopping performance [31, 32]	Mean or median limb symmetry index	12 months
Quadriceps and hamstrings strength	Mean or median limb symmetry index	12 months
Adherence to rehabilitation	Number of sessions completed	Every 2 weeks while completing rehabilitation
Adherence to BANG intervention	Number of completed video and audio sessions	6 months

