#### Reclassifying variables

For new knee injuries, we plan to classify the collected data into three dichotomous variables for analysis: (i) new knee problem (based on all complaints), (ii) new ACL injury (either knee), (iii) new knee injury treated with surgery. The trial co-ordinator will check all injury registration reports as they are completed and returned by participants. If additional information (e.g. injury diagnosis and treatment) is required, a blinded researcher will contact the participant by phone or text message, and/or review the participant’s medical record (Additional file 1).

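### Read literally, a two-week look-back with four-weekly or monthly registration leaves about half of year 2 outside the sport and knee-injury questions, and the two injury outcome lists differ

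*Protocol article*

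**What the plan says.** **Spacing of registrations.** The abstract (Methods) states: "Physical activity participation and new injuries are self-reported every two weeks for 12 months, then every 4 weeks to 24 months follow-up". Table 2, in its rows for sports participation and new knee injuries, has "Every 2 weeks to 12-months follow-up; every month from 12 to 24 months follow-up". The Fig. 1 caption also describes year-2 registration as monthly.

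**Look-back.** Under Secondary outcome measures: new knee injuries, the protocol says "Participants self-report any new knee problems that have occurred during the registration period (preceding two weeks". Under Secondary outcome measures: sports participation, it concerns activities "they participated in during the registration period (preceding two weeks". Neither section limits the two weeks to year 1, and no other section shown gives a year-2 window.

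**Injury outcomes.** Table 2 aggregates new injuries as "Proportion of participants who report a new (i) ACL injury, (ii) meniscus injury, (iii) other knee injury or problem". The section Reclassifying variables plans three dichotomous analysis variables: "i) new knee problem (based on all complaints), (ii) new ACL injury (either knee), (iii) new knee injury treated with surgery".

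**Analysis.** Under Planned secondary analyses: time-varying analyses, sports participation and new knee injury are compared by generalised estimating equations with group, site and assessment time point as fixed factors.

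**The concern.** A look-back shorter than the spacing of the registrations leaves gaps. In year 1 the two match. In year 2 the spacing roughly doubles and the stated look-back does not change, so an injury in the uncovered weeks falls outside the question as worded.

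Nothing else described in the article closes that gap. The open-ended adverse-event question (Harms) is sent only in the first year. The telephone, text and medical-record follow-up (Reclassifying variables) serves to complete injury reports already returned; it is not described as a search for unreported ones.

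This matters because the section Issues related to adverse events acknowledges that an app designed to raise return to sport could also raise new knee injuries. The control return rate assumed at one year is 33% (Sample size calculation), so much sport exposure plausibly falls in year 2, where literal coverage is weakest.

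The two injury lists add a smaller problem: the set of results that will describe this harm is not stated consistently.

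**Working it through.** The protocol gives no coverage figure to reproduce, so the check starts from its stated intervals.

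**Inputs.** The look-back is 2 weeks (both outcome sections). The interval is 2 weeks in year 1, and in year 2 either 4 weeks (abstract) or one month (Table 2, Fig. 1 caption). One year is 365.25 / 7 = 52.18 weeks.

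**1. Coverage on the literal reading.** Covered share = registrations × 2 weeks / 52.18.

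| Period | Registrations | Weeks covered | Covered | Not covered |
|---|---|---|---|---|
| Year 1, every 2 weeks | 26 | 52 | about 100% | about 0% |
| Year 2, every 4 weeks | 13 | 26 | 50% | 50% |
| Year 2, monthly | 12 | 24 | 46% | 54% |

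With a look-back equal to the interval, coverage in year 2 would be about 100%.

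**2. What this could do to recorded injuries (illustration).** The documents give no year-2 injury risk, so a range is assumed. Assume also a constant hazard, and that an injury in an uncovered week is never reported. The recorded risk is then 1 − (1 − r)^f, where r is the true risk and f the covered share.

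| Assumed true year-2 risk | Recorded, f = 0.50 | Recorded, f = 0.46 |
|---|---|---|
| 5% | 2.5% | 2.3% |
| 10% | 5.1% | 4.7% |
| 20% | 10.6% | 9.8% |

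With the protocol's 15% drop-out, 222 × 0.85 = 189 participants remain. At a 10% risk about 19 would be injured. Those not recorded would number 189 × (0.10 − 0.051) ≈ 9 to 189 × (0.10 − 0.047) ≈ 10. For rare events the standard error of a log odds ratio varies with one over the square root of the event count. For year 2 it would therefore grow by about √(10/5.1) = 1.4 to √(10/4.7) = 1.5. Only the year-2 part of a 24-month proportion is affected.

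**3. If the year-2 form covers the whole interval.** Suppose the arms differ by d minutes of sport per week throughout. The difference in a registered total is 2d in year 1, and in year 2 either 4d (four-weekly) or 52.18/12 = 4.35 times d (monthly). A simple average over complete registrations with equal weights gives:

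- four-weekly: (26 × 2d + 13 × 4d) / 39 = 104d / 39 = 2.67d
- monthly: (26 × 2d + 12 × 4.35d) / 38 = 104.2d / 38 = 2.74d

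Neither is a difference per two weeks, per four weeks or per month. A time-point factor takes up the common jump in level but does not put the group difference on one scale. For injuries, the odds per registration roughly double when the interval doubles. The odds ratio changes less, because for rare events it stays close to a ratio of rates.

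**4. The injury lists side by side.**

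| Outcome | Table 2 | Reclassifying variables |
|---|---|---|
| ACL injury | yes | yes (either knee) |
| Meniscus injury | yes | not separately |
| Other knee injury or problem | yes | not separately |
| Any new knee problem | no | yes |
| Surgically treated injury | no | yes |

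Only ACL injury is in both.

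**The case against.** The best defence is that the parenthesis merely explains the term registration period. Such a period is naturally the interval that each registration covers, so two weeks may describe only the year-1 form. The year-2 form may be in Additional file 1, which is not shown. This stands, and it rules out the inference a reader might draw that half of year 2 is in fact unobserved. It does not remove the point: on that reading the two outcome sections are incomplete and the scale problem in step 3 arises.

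Second, a reader might take the coverage figure as the share of injuries lost, for example 11 of 22 from 222 × 0.10 × 0.5. That is an upper bound on an assumed rate, and it ignores the 15% drop-out. A participant with an ACL rupture, or with a problem that persists or is still being treated, may well report it at the next registration whatever the wording, particularly under an all-complaints definition. The share of affected participants missed could be well below the share of weeks uncovered.

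Third, a reader might infer bias between the arms. The gap is the same in both, so it lowers proportions and precision; nothing in the documents suggests that it favours one arm. For sport minutes, two weeks out of four is a usable sample of exposure, so the loss is smaller there than for incident injuries.

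Fourth, it would be wrong to say that meniscus injuries drop out of the analysis. The all-complaints variable includes them. The section on reclassification also presents itself as the derived analysis set, which limits the freedom to choose between lists. What remains is that Table 2 announces outcomes the analysis variables do not report separately, and omits one that they add.

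**Conclusion.** The point holds as an inconsistency in the stated plan. On the literal wording, 50% (four-weekly) to 54% (monthly) of year-2 time lies outside any look-back for sport and new knee injuries, and no other year-2 source described in the article fills it. The likely consequence would be under-recorded injuries in year 2, similar in both arms, and less precision on the trial's named possible harm. The size of that loss cannot be fixed from the documents: the figures in step 2 rest on assumed risks and on missed injuries never being reported later.

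On the alternative reading nothing is missed, but year-1 and year-2 minutes, and injury odds per registration, are on different scales in one model. Either way the text needs a change. The disagreement between four weeks and a month, 13 against 12 registrations, is a further small inconsistency.

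The 12-month primary outcome and all year-1 registrations are unaffected. So is substitution of a missing primary outcome (Missing data), which draws on the fortnightly sport data. The mismatch between the injury lists is real but modest.

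**What to change.** - State one year-2 interval, either four weeks or a month, in the abstract, Table 2 and the Fig. 1 caption.
- From month 12, word the sport and injury questions as covering the time since the last registration. If the app already does this, say so in the two outcome sections.
- Analyse sport as minutes per week covered, and allow for interval length in the injury model, for example with a term for time covered.
- Record which look-back applied to each participant who entered year 2 before any change.
- Align Table 2 with Reclassifying variables so that one injury list is fixed before analysis, stating whether meniscus injury is reported separately.

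**Cost.** A short text change in the app and a few lines of analysis wording. Recall becomes somewhat longer in year 2. Recruitment began in June 2019 and the article appeared in August 2020, so the earliest participants may already have passed month 12. If their form did ask about two weeks, look-backs would be mixed within year 2, which is why the applicable window should be recorded.

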#### Secondary outcome measures: *patient-reported outcomes*

To assess *psychological readiness to return to sport*, we use the condition-specific ACL-Return to Sport after Injury (ACL-RSI) scale – a 12-item scale, scored from 1 to 10; higher scores indicate greater psychological readiness to return to sport [38].

To assess *self-efficacy*, we use the *future* domain of the Knee Self-Efficacy Scale (K-SES) [25]. The domain comprises 4 questions to assess self-efficacy related to future knee function: (1) how certain are you that you can return to the same physical activity level as before the injury?, (2) how certain are you that you would not suffer any new injuries to your knee?, (3) how certain are you that your knee would not ‘break’?, (4) how certain are you that your knee will not get worse than before surgery? Each question is scored on a 0 to 10 scale. The domain score is the mean of responses to the 4 questions, and higher scores represent stronger self-efficacy.

For *motivation to return to sport*, we ask 3 questions, all measured on a 1 to 10 scale [26]: (1) how important is it for you to return to the same sport or recreation activity as before your knee injury?, (2) do you think it is possible for you to return to the same sport or recreation activity as before your knee injury?, (3) how much time and effort are you willing to invest to return to the same sport or recreation activity as before your knee injury?

To assess *quality of life*, we use the ACL-Quality of Life (ACL-QoL) scale [27] – a 32-item questionnaire, scored from 0 to 100; higher scores indicate greater knee-related quality of life. The ACL-QoL is the only condition-specific measure of quality of life available for people with ACL injury.

For *patient-reported knee function*, we use the Single Assessment Numeric Evaluation (SANE) [29] (“On a scale from 0-100 where 100 represents the best, what number would you give your knee today?”) and the International Knee Documentation Committee (IKDC) subjective knee form, [28] a 19-item condition-specific measure. The SANE and the IKDC subjective knee form measures are both scored out of 100 points, with a higher score indicating superior self-reported knee function.

For *functional knee stability*, we use ask participants to report (i) how many times (if any) their knee has given way after surgery, and (ii) how often their knee gives way.

#### Secondary outcome measures: clinician-measured knee function

For quadriceps and hamstrings strength, we use an isokinetic dynamometer to record concentric peak torque in a seated position. We measure 5 repetitions at 60°/sec and 15 repetitions at 180°/sec.

For hopping performance, we use three different tests (Fig. 3) [31, 32]. The single hop for distance test is the maximum distance the person can hop from a stationary starting position. The triple hop for distance test is the maximum distance the person can hop with three successive hops from a stationary starting position. The side hop test is the number of hops the person can complete side-to-side (minimum width 40 cm), in a 30-s period.

**Fig. 3 Fig3:**
[figure not shown]
Visual summary of hopping performance tests

For knee effusion, we use the stroke test [30] to grade the amount of knee effusion as no fluid wave, trace (small fluid wave), 1+ (large fluid wave), 2+ (fluid wave spontaneously returns to the medial aspect of the knee) or 3+ (excess fluid that cannot be moved away from the medial aspect of the knee).

#### Secondary outcomes measures: *adherence*

We will assess adherence to the Back in the Game intervention during the 24-week intervention period by counting page views for different types of content (e.g. Vimeo analytics for video content, SoundCloud analytics for audio content). We will assess adherence to rehabilitation every two weeks by asking participants to report the number of supervised physiotherapy sessions, number of home-based exercise sessions and the number of gymnasium-based exercises sessions completed in the previous two weeks.

### Assignment of interventions: allocation—sequence generation

We use a cluster-randomisation strategy. An independent statistician created a computer-generated randomisation schedule for each clinical site (hospitals that belong to the same clinical network are classified as one clinical site for randomisation) using computer-generated random numbers in blocks of 6. We use block randomisation because we expect faster recruitment rates at the high-volume private metropolitan clinical centres.

### Allocation—concealment mechanism

Allocation is concealed in sequentially numbered, opaque, sealed envelopes. When the central study co-ordinator is notified that a participant has consented to participate in the study, she opens the next envelope in the sequence. Allocation is managed at a location remote to the clinical sites.

### Blinding

Outcome assessors and data analysts are blinded after assignment to intervention. Because the Back in the Game app is a self-directed intervention and designed as a standalone to usual rehabilitation care, there are no additional care givers who should be blind to participant allocation.

Baseline data are collected via the smartphone app, prior to allocation and the intervention commencing. Before they accept participation, all participants are informed that (1) they will receive content guiding them about returning to sport via the smartphone app, and (2) that depending on which group they are allocated to, they will receive more or less content. We do not provide further description of the intervention prior to participants consenting to participate, to avoid inducing participation. Participants are informed that if they agree to be in the trial, there is a 50–50 chance of receiving more than the usual amount of content about return to sport provided during post-operative rehabilitation. Participants are not informed of their group allocation, but we cannot assume they remain blinded to group allocation.

When they return for clinical assessment at 12 months follow-up, we will ask participants not to discuss the amount and content of information they received during post-operative rehabilitation with the outcome assessor. We plan multiple strategies to minimise the chance of a participant inadvertently disclosing allocation to the outcome assessor including sending the participant a reminder SMS message one day prior to the follow-up visit.

### Informed consent

The clinical co-ordinator provides a description of the trial to patients (written and verbal information) and discusses the information provided. After the eligibility screening process, patients can verbally consent to participate in the trial and be contacted by the trial co-ordinator. Patients provide electronic informed consent through the software platform used for all study data collection.

### Sample size calculation

There are no trials of psychological support interventions aimed to help athletes return to sport following sports injury, so it is difficult to accurately estimate the expected effect size for our trial. We calculated the same size required to detect a between-group difference in return to preinjury sport rate of 20% at 1 year. We assumed a base return to sport rate of 33%, [39] a two-sided alpha of 0.05, beta of 0.2, and a drop-out rate of 15%. The required sample size is 222 participants (111 in each group).

### Data collection

All participants download the Back in the Game app, which is how we deliver the intervention, and administer all research data collection. Participants in the experimental group have access to a separate part of the app that only goes ‘live’ when the intervention commences. Participants in the control group cannot see the ‘hidden’ intervention part of the app.

Baseline measurements are collected prior to allocation. Participants complete the baseline questionnaire in the week prior to ACL reconstruction surgery, providing demographic information, sports participation, and a baseline measure of self-reported knee function, self-efficacy, and anxiety and depression (Table 3). The Internet-delivered intervention commences in the first post-operative week (Table 4). Permissions to access the intervention can only be assigned at the time the participant sets up their own profile in the app and provides informed consent.

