### Interventions

The Back in the Game app and usual rehabilitation care are summarised according to the Template for Intervention Description and Replication (TIDieR) Checklist [21] (Table 1). All participants complete post-operative rehabilitation as normal. As part of usual rehabilitation care in Sweden, patients typically receive generic written information about knee injury and surgery, recovery in the early post-operative period, return to sport, and injury prevention. A summary of the typical written information patients receive from their treating clinician is delivered to both groups via the smartphone application. The Back in the Game app intervention delivers additional, tailored information and cognitive-behavioural therapy exercises to complement post-operative rehabilitation.

**Table 1 Tab1:** Overview of usual rehabilitation care (control) and the Back in the Game intervention (experimental). All participants receive usual post-operative rehabilitation care

TIDieR item	Control	Experimental
**Name**	Usual post-operative rehabilitation care	Back in the Game plus usual post-operative rehabilitation care
**Why**	Usual care reflects the real-world clinical context. Rehabilitation helps patients recover from surgery, gradually regain knee function, and prepare to return to sport.	Psychological factors such as confidence and anxiety about new injury, have strong influences on returning to sport after serious knee injury. Rationale: supporting psychological readiness to return to sport, in addition to usual rehabilitation, will help athletes transition back to their sport. A self-directed approach will help target the specific challenges encountered by the individual.
**What (materials)**	Strength training equipment (e.g. free weights, machine weights, resistance bands, suspension cables), balance training equipment (e.g. BOSU ball) and aerobic training equipment (e.g. treadmill, stationary bicycle) as available in the usual care setting.	All content is provided on-demand through the Back in the Game smartphone application (see https://vimeo.com/345486299/6bba07cc11 for an overview [in Swedish]).

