Limb symmetry index is calculated using the formula: $$ \frac{involved\ limb}{uninvolved\ limb}\times 100 $$; ACL, anterior cruciate ligament

**Table 3 Tab3:** Baseline participant characteristics

Variable	Aggregation
Time from injury to surgery	median (IQR)
Age at injury	mean (SD)
Sex	
Female	n (%)
Male	n (%)
Primary occupation	
Student	n (%)
Desk work	n (%)
Manual work	n (%)
Heavy manual work (e.g. construction)	n (%)
Unemployed	n (%)
Preinjury sports participation	
Contact, pivoting sport	n (%)
Non-contact, pivoting sport	n (%)
Return to sport goal	
Return to same sport	n (%)
Return to different sport	n (%)
Return to sport expectations	
Within 1 month	n (%)
Within 6 months	n (%)
Within 12 months	n (%)
After 12 months	n (%)
IKDC subjective knee form [28] score	mean (SD)
General Self-efficacy Scale [33] score	mean (SD)
Knee Self-Efficacy Scale [25] *Future domain*	mean (SD)
Hospital Anxiety & Depression Scale [34] score	mean (SD)

*IQR* interquartile range, *SD* standard deviation, *IKDC* International Knee Documentation Committee

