#### Planned secondary analyses: time-varying analyses

We will compare psychological readiness to return to sport (ACL-RSI), motivation to return to sport, self-reported knee function (SANE and IKDC), sports participation and new knee injury between treatment groups using generalised estimating equations. Group, clinical site, and assessment time point will be included as fixed factors. If baseline values were collected, we will also include the baseline value in the relevant model as a covariate. For continuous variables, we will calculate mean difference and 95% confidence intervals. For dichotomous variables, we will calculate the odds ratio and 95% confidence intervals.

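### ACL-RSI, the scale for the app's stated rationale, has no pre-allocation value (nor do SANE and motivation), so the conditional baseline-covariate rule cannot apply to it and precision on secondary comparisons is lost

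*Protocol article*

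**What the plan says.** All references are to the Protocol article.

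- **Rationale.** Table 1 (Interventions) explains the app this way: "supporting psychological readiness to return to sport, in addition to usual rehabilitation, will help athletes transition back to their sport". For that construct, the section on patient-reported outcomes says "we use the condition-specific ACL-Return to Sport after Injury (ACL-RSI) scale".
- **Baseline content.** Data collection describes a questionnaire completed before allocation, in the week before surgery, with demographics, sports participation and "a baseline measure of self-reported knee function, self-efficacy, and anxiety and depression (Table 3". Table 3 names the scales: IKDC, General Self-efficacy, the K-SES future domain, and, as its last row, "Hospital Anxiety & Depression Scale [34] score". It has no row for ACL-RSI, SANE or motivation.
- **Follow-up times.** Table 2 gives ACL-RSI at "3, 6, 9, 12, 24 months" and motivation at 3, 6 and 9 months. SANE is collected fortnightly and later monthly during follow-up. The Abstract agrees that the patient-reported scales "are also assessed at 3, 6, 9, 12 and 24 months after surgery".
- **Analysis.** The time-varying analyses begin "We will compare psychological readiness to return to sport (ACL-RSI), motivation to return to sport, self-reported knee function (SANE and IKDC" and continue with sports participation and new knee injury. Their covariate rule is "If baseline values were collected, we will also include the baseline value in the relevant model as a covariate".

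**The concern.** The questionnaire given before allocation covers anxiety, depression and two kinds of self-efficacy, but not the construct the app is meant to move. The first ACL-RSI score arrives when roughly half of the programme has been delivered, so no readiness score is free of treatment.

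Three things follow. The baseline-covariate rule has nothing to work on for ACL-RSI, SANE or motivation; of the patient-reported scales in those models, only IKDC can use it. The comparability check in the Statistical analysis plan section runs on Table 3 variables, so an imbalance in readiness itself would not be seen. And change in readiness from before treatment cannot be described. At stake is the precision and the ease of interpretation of the secondary outcome closest to the app's rationale.

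**Working it through.** **1. The plan's own figure.** The only stated sample size is 222, for the primary binary outcome. With 33% against 53%, two-sided alpha 0.05 and 80% power, the pooled formula is

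n = [1.960·√(2·0.43·0.57) + 0.842·√(0.33·0.67 + 0.53·0.47)]² / 0.20² = 95.0005, rounded up to 96 per arm.

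Multiplying by 1.15 gives 110.4, so 111 per arm and 222 in total, as stated. (Dividing by 0.85 gives 113 per arm, 226 in total.) ACL-RSI does not enter this calculation. The plan states no precision for ACL-RSI.

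**2. Timing.** Three months is about 13 weeks. The app starts in the first post-operative week, so about 12 of 24 weeks have passed at the first ACL-RSI score: half.

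**3. Value of a baseline on everyone, single visit.** With baseline-to-follow-up correlation r, adjustment multiplies residual variance by 1 − r². The analysed number is 111 × 0.85 ≈ 94 per arm. The unadjusted detectable difference at 80% power is (1.960 + 0.842)·√(2/94) = 0.409 SD. The documents give no r, so a range is assumed.

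**4. What can still be recovered.** Recruitment runs from June 2019 to December 2020, 19 calendar months, and the article is dated 8 August 2020. About 4.75 months remain, and 4.75/19 = 0.25. Assuming even accrual, a quarter of participants could supply a baseline, and average residual variance becomes 1 − 0.25·r².

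| r (assumed) | Variance cut, baseline on all | SE cut | Detectable difference | Variance cut, baseline on a quarter | SE cut | Detectable difference |
|---|---|---|---|---|---|---|
| 0.3 | 9% | 4.6% | 0.390 SD | 2.3% | 1.1% | 0.404 SD |
| 0.4 | 16% | 8.3% | 0.375 SD | 4.0% | 2.0% | 0.400 SD |
| 0.5 | 25% | 13.4% | 0.354 SD | 6.3% | 3.2% | 0.396 SD |
| 0.6 | 36% | 20.0% | 0.327 SD | 9.0% | 4.6% | 0.390 SD |

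**5. Average over the five ACL-RSI visits.** The listed fixed factors are group, site and time point, so an averaged effect is also relevant. If one correlation r holds between all visits including baseline, the variance factor is (1 + 4r)/5 without adjustment and (1 + 4r)/5 − r² with it. At r = 0.3 this is 0.44 against 0.35 (SE cut 10.8%); at r = 0.5, 0.60 against 0.35 (SE cut 23.6%). With a baseline on a quarter, r² is replaced by 0.25·r² and the SE cuts fall to 2.6% and 5.4%. A pre-surgery score that correlates less with follow-up than the follow-ups do with each other would yield less.

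**6. K-SES as a substitute covariate.** If baseline K-SES future score correlates s with follow-up ACL-RSI, it cuts single-visit variance by s² in everyone. Setting s² = 0.25·r² gives s = r/2. So K-SES needs only half the correlation of an ACL-RSI baseline to match a baseline obtained from a quarter of participants: s = 0.2 gives 4%, the same as r = 0.4 in the table.

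**The case against.** The strongest reply is that nothing here is stated wrongly. The covariate rule is explicitly conditional and works for IKDC. That stands: a reader might infer that the plan promises an adjustment it cannot make, or contradicts itself, and the text supports neither.

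Second, allocation is randomised and stratified by site, so the ACL-RSI comparison is unbiased without a baseline score. That stands as well.

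Third, a reader might say that the trial's test of mechanism is undermined. No mediation or mechanism analysis is planned; these are secondary between-group comparisons with no claimed power.

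Fourth, motivation should not be treated like readiness. It is not among the seven modules, and eligibility requires intent to return to sport, which may narrow its baseline range. This is largely right, although recovery expectations are named as a target in the Discussion and one motivation item asks whether return is thought possible. The case rests on ACL-RSI.

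Fifth, related measures are collected: K-SES future, General Self-efficacy, anxiety and depression, and return-to-sport goal and expectations. They give an indirect view of balance, and change from 3 months onward can still be described. True, but none of these measures is listed as a covariate for ACL-RSI, apart from the provision for regression adjustment after a major imbalance.

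Last, Table 4 and Additional file 1 are not shown, so a baseline ACL-RSI entry cannot be wholly excluded. Tables 2 and 3 and the text all point the other way.

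**Conclusion.** The point holds as a design weakness of modest size. On the text shown, readiness is not measured before allocation, so a planned and sensible adjustment cannot reach the outcome nearest to the app's rationale, and balance in readiness cannot be checked directly. The primary outcome and its sample size are not involved.

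It would be tempting to present the full-baseline column of the table as what an amendment would gain. It is not: that column describes what was forgone by not measuring at the start, whereas the quarter column describes what new questionnaire items could still return. Both depend on an assumed correlation, and the second also on even accrual and on the publication date as the point from which items could be added. Slower accrual than planned would leave more to gain. The K-SES covariate does not depend on accrual, but its correlation with ACL-RSI is likewise not given.

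**What to change.** 1. In the time-varying analyses, prespecify the baseline K-SES future score as a covariate in the ACL-RSI model. Every participant is asked for it before surgery, so this needs no new data: one sentence, fixed before unblinding.
2. As a cheap addition, put the 12 ACL-RSI items and the single SANE item into the pre-surgery app questionnaire for participants still to be enrolled. Use the scores under the existing covariate rule, with a missing-baseline indicator for those already enrolled. Because missingness would be set by enrolment date, before allocation, the indicator does not bias the group comparison.

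The cost is thirteen items, a few minutes of extra burden per participant, and an amendment to the questionnaire. Participants already enrolled will still have no pre-treatment readiness score, so any description of balance or change from baseline should be labelled as applying to the later enrolees only.
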